#### **4.2.3.2 Workshop 2**

We will reconvene participants from Workshop 1 and present them with the training program (addressing the interpreting domains), the training structure (addressing preferred teaching format), and the simulation scenario (through which the impact of the training will be assessed). After each component of the training is presented, Participants will be divided into

mixed break-out rooms, and asked to comment on the proposed training content, identify the value proposition of the training, and develop the key messages most effective at explaining the training. Detailed recordings and notes from the workshops will be collected by the research team, compiled into one central list, and used to refine the training modules.

### **4.3 *Development of training and education materials***

The research team will use ideas and feedback generated during the co-design workshops to develop the training package. Training will comprise 3-5 modules of 3-4 hours duration, incorporating multimedia and text-based learning as well as didactic and interactive learning (e.g. lectures, quizzes etc.). CIs [name], [name], [name], and [name] have experience in developing and implementing dementia training, CIs [name] and [name] in interpreter training, and CI [name] in simulation training for health professionals. The training content and the simulation script, which will be used to assess the training, will be developed by the research team. It will then be operationalised for an online learning environment by web architects (Elbury e-learning), designers ([name]), and filmmakers (Fire Films) with whom we have ongoing links through our related CALD-dementia studies.

### **4.4 *User testing***

Once the online training and simulation assessments have been developed, they will be user-tested by 10 interpreters as part of process evaluation.

#### **4.4.1 Participants**

10 interpreters will be recruited for user testing through our interpreter industry partners, TIS National, who will use their internal mailing lists to issue calls for expressions of interest with contact details of the research team. To be eligible, interpreters must be NAATI credentialed with provisional certification or professional certification and 6+ months practicing experience. Interpreters will be remunerated by our industry partners according to a standard hourly interpreting rate for time spent participating in user-testing.

#### **4.4.2 Method**

Interpreters will undertake the training including the simulation assessment. Using the thinking-aloud method [26] and a 60-minute exit survey, we will assess how long the training takes to complete, its acceptability, including most/least relevant and helpful aspects, the main barriers and facilitators of using the online platform, and elicit any recommended improvements. These assessments will be undertaken by researchers at NARI and RMIT.

A bespoke survey questionnaire will be developed for the assessments based on the training modules' content and guided by the Unified Theory of Acceptance and Use of Technology [27]. The survey will assess direct determinants of intention. These include: performance expectancy (the degree to which using the training will provide benefits in performing an interpreting role), effort expectancy (the degree of ease associated with the use of the training), and social influence (the degree to which an interpreter perceives that others important to them believe they should complete this training).

This process evaluation in combination with the research team's observations and partners' industry experiences will be collated to finalise the training modules for trial evaluation, implementation, and roll-out.

## 5 Study 2 – Randomized control trial of training

Study 2 will be a randomized control trial (RCT), conducted to evaluate whether the training package developed during Study 1 fulfils our primary project aim of improving the quality of interpreter communication in a cognitive assessment for dementia. The trial will be a 6-month wait-list RCT with a parallel design, conducted with a target of 150 interpreters in equal allocation (75 in the intervention group and 75 in the control group).

Outcomes will be assessed at baseline ( $t_0$ ), post-intervention (3m after baseline;  $t_1$ ) and follow-up (6m after baseline;  $t_2$ ). The baseline covariates will include characteristics of interpreters (age; sex; ethnicity; location; educational and economic attainments; and NAATI credential status).

### 5.1 *Participants*

150 interpreters will be recruited for the trial through our interpreter industry partners, NAATI and AUSIT, who will use their internal mailing lists to issue calls for expressions of interest with contact details of the research team. To be eligible, interpreters must be:

- a) NAATI credentialed with provisional certification or professional certification;
- b) Have 6+ months practicing experience;
- c) Have access to an internet connection;
- d) Interpret for Greek, Italian, Mandarin, Cantonese, Arabic or Vietnamese languages; and
- e) Not participated in study 1 (in either the workshops or the user-testing).

### 5.2 *Randomisation*

Interpreters will be randomised into:

- a) an intervention group ( $n=75$ ) who will use the training package for 6m immediately following the randomisation, or
- b) a wait list control group ( $n=75$ ) who will receive access to the training package six months after randomisation.

This approach was chosen because it involves no deception of participating interpreters, and because both groups of interpreters will eventually have access to the training.

After enrolment in the trial, and before randomisation, participants will complete the simulated battery to measure the primary outcome of quality of interpreted communication. The test outcome will not be provided to the person until an external statistician has done the randomisation procedure (randomisation by minimisation). A researcher at National Ageing Research Institute will provide the test outcome and randomisation outcome (test/control) to the person approximately one week after doing the simulated tests. This ensures that randomisation outcome is independent of baseline scores. In this pragmatic trial, it is not possible to blind participants to group allocation when collecting the post-intervention scores. Hence, this trial is a single-blinded study where outcome assessors will be blinded to allocation.

### 5.3 *Intervention*

Interpreters in the intervention group will have access to the intervention for 3 months from immediately after randomisation. Adherence is defined as a participant completing 70% of the training. The wait list control group will receive access to the training after completing the 6-

month assessment ( $t_2$ ). All those who complete the training package will receive Continuing Professional Development points that count towards NAATI interpreter certification.

#### 5.4 Outcome measures

Our primary outcome is the quality of interpreted communication measured via a battery composite  $z$  score evaluating six interpreting domains [24, 25] crucial to communication quality (Table 2). These measures will be collected using questionnaires, scenario response testing and video footage of a virtual simulated patient consultation. Simulation pedagogy is a core element of clinical training in health professional education [28] as it provides a structured and safe environment allowing performance review and development. Simulations have been used to evaluate practice in interpreter studies [29].

Table 2: Quality of interpreted communication measured via a battery composite  $z$  score

| Domains                                                                                                                                                           | Measures                                                                                                                                                                                                             | Collected via                                            |
|-------------------------------------------------------------------------------------------------------------------------------------------------------------------|----------------------------------------------------------------------------------------------------------------------------------------------------------------------------------------------------------------------|----------------------------------------------------------|
| 1. Pre-interactional briefing with clinician; explanation of role to clinician and limited English proficiency client                                             | Simulations to be developed based on input from co-design, literature review, and Mental Health Interpreting Guidelines for Interpreters [30]                                                          | Video footage rated by an experienced interpreter        |
| 2. Accurate and complete bi-directional meaning transfer inter-lingually; interactional management skills; rhetorical skills; linguistic competency and accuracy. | Simulations to be developed based on input from co-design, literature review, NAATI Certified Interpreter Test Assessment Rubrics [31] and Mental Health Interpreting Guidelines for Interpreters [30] | Video footage rated by an experienced interpreter.       |
| 3. Knowledge of medical terminology                                                                                                                               | Dementia-Knowledge Assessment Scale[28]                                                                                                                                                                              | Questionnaire                                            |
| 4. Knowledge of dementia diagnosis scales and dementia-related services.                                                                                          | Simulations and questions to be developed based on co-design and literature review.                                                                                                                    | Questionnaire and video footage                          |
| 5. Working ethically with clinicians and people living with dementia                                                                                              | Simulations and scenarios to be developed based on input from co-design, literature review, AUSIT code of ethics[29] and Mental Health Interpreting Guidelines for Interpreters [30]            | Scenario-response test and video footage                 |
| 6. Demonstration of intercultural competency                                                                                                                      | Simulations , scenarios and questions to be developed based on input from co-design and NAATI Intercultural Competency Text Rubrics [32]                                                        | Questionnaire, scenario response test, and video footage |

As the content of the video simulations and questionnaires depend upon input gathered through interviews and workshops during study 1, the measures will be developed after study 1 is complete. CIs [name] and [name], who both have expertise in the training and assessment of interpreters, will lead development of measures. They will ensure measures adhere to NAATI assessment standards and relevant interpreter ethical guidelines. Once the

measures have been fully developed, they will be submitted to the HREC for approval as an amendment prior to any study 2 data being gathered.

In our study, the simulation of ~40 minutes will mimic a typical cognitive assessment of a CALD patient at CDAMS/ACAS (Box 1). The patient and clinician's dialogue will be uniform, pre-scripted, and filmed in the top six languages spoken by older CALD Australians: Greek, Italian, Mandarin, Cantonese, Vietnamese, and Arabic. The interpreter's dialogue is not scripted, and they will be required to interpret and facilitate the assessment as they would in a standard consultation. Interpreters will be asked to click a video record button to record their online simulated consultation (similar to how Zoom meetings are recorded). These simulations will be automatically saved and uploaded, ready for assessment. After completing the simulation, interpreters will complete the questionnaires. Video footage and the questionnaires will be assessed by blinded assessors who are NAATI examiners, seasoned in applying this assessment model regularly. To ensure rigour, CI [name] will train the assessors about the assessment items and each assessor will have their first four assessments double assessed to check for inter-rater reliability. In scenarios where components of the simulation are missing or incomplete, assessors will only award marks to the overall score for sections of the cognitive assessment that were interpreted. Failure to interpret the introductory or concluding component of the assessment will not affect the score.

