#### Box 1: A standard CDAMS/ACAS

- Case briefing between the clinician and interpreter (5mins)
- Introduction to the patient (5mins)
- Interpretation of the RUDAS (15mins)
- Ask about medical issues, mood etc. (5mins)
- Next steps (5mins)

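### The exemption of the introductory and concluding components from scoring is not limited by domain, so it can reach the briefing and role explanation that form Domain 1 of the primary composite

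*Protocol*

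**What the plan says.** Protocol Section 5.4 defines the primary outcome as quality of interpreted communication, "measured via a battery composite $z$ score evaluating six interpreting domains". In Table 2 the first domain is "Pre-interactional briefing with clinician; explanation of role to clinician and limited English proficiency client". Its only listed source is "Video footage rated by an experienced interpreter"; no questionnaire or scenario test is attached to it.

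Box 1 lists the parts of the simulated consultation in order: a case briefing with the clinician, the introduction to the patient, the RUDAS, questions on medical issues and mood, and next steps.

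Two scoring sentences follow in the text of Section 5.4. For simulations with missing or incomplete components, "assessors will only award marks to the overall score for sections of the cognitive assessment that were interpreted". The next sentence adds: "Failure to interpret the introductory or concluding component of the assessment will not affect the score".

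Section 5.4 also says that the content of the measures will be developed after Study 1 and sent to the ethics committee as an amendment before Study 2 data are gathered. Each assessor's first four assessments are to be double assessed.

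**The concern.** The exemption is worded for the score as a whole. It names no domain, and the protocol does not say which items of Box 1 count as introductory or concluding. Domain 1 consists of things an interpreter does at the opening of the encounter. An assessor who applies the sentence literally to an interpreter who skips the opening has no clear basis for a low Domain 1 mark, although Table 2 makes that behaviour one of the six things measured.

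This is a scoring rule for the primary endpoint. If the exemption prevails, some failures in a named domain go unrecorded. If some assessors apply it to Domain 1 and others do not, the scores carry extra between-assessor variation. Double assessment of the first four recordings per assessor may not reveal this, since the rule matters only when an opening is omitted. Once recordings have been scored under different readings, choosing one afterwards is no longer a neutral decision.

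**Working it through.** **Comparing the texts**

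| Question | Where | Answer |
|---|---|---|
| Is the opening behaviour part of the primary outcome? | Table 2, row 1 | Yes: clinician briefing, and role explanation to clinician and client |
| What is it scored from? | Table 2, row 1 | Simulation video only |
| Where in the simulation would it occur? | Box 1 | Case briefing (5 min) and introduction to the patient (5 min) |
| What if a section is not interpreted? | Section 5.4, first scoring sentence | Marks only for sections that were interpreted |
| What if the introduction or conclusion is not interpreted? | Section 5.4, second scoring sentence | No effect on the score |
| Is the exemption limited by domain, or its scope defined? | Section 5.4 | No |

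Table 2 row 1 does not use the word introduction. The link from Domain 1 to the introductory component runs through Box 1, and it is an inference from where a briefing and a role explanation would take place.

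**Extent**

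Box 1 adds to 5 + 5 + 15 + 5 + 5 = 35 minutes. The two opening items are 10 of 35 minutes and the closing item is 5 of 35. If the six domains carried equal weight (an assumption; no weights are given), Domain 1 would be 1/6 of the composite.

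**The planned sample size, for context**

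Inputs from Section 5.5: difference 1.3, SD 2.5, alpha 0.05, power 80%. Sidedness is not stated; two-sided is assumed here.

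n per arm = 2 × (1.960 + 0.842)² × 2.5² / 1.3² = 58.05, rounded up to 59, so 118 in total. This agrees with the stated 120. With d = 1.3/2.5 = 0.52, a two-sample t-test has power 81% at 60 per arm and 89% at 75 per arm. The present point changes none of these figures.

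**How far an illustration can be pushed**

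Suppose Domain 1 carried no treatment effect for any participant, with equal weights and equal effects across domains. The answer then depends on what is assumed about variance:

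- SD of the composite unchanged: d = 0.52 × 5/6 = 0.433; power 65% at 60 per arm, 75% at 75 per arm.
- Domain 1 removed together with its variance, domains of equal variance with common correlation ρ: d = 0.52 × √[5(1 + 5ρ) / (6(1 + 4ρ))].
  - ρ = 0: d = 0.475, power 73% at 60 per arm
  - ρ = 0.3: d = 0.506, power 78%
  - ρ = 0.5: d = 0.513, power 80%

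Both versions overstate the rule's reach. It operates only when the opening is not interpreted; openings that are performed can still be rated. The figures show how strongly the result depends on assumptions and are not estimates of a loss.

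**The case against.** The strongest reply is that the exemption concerns failure to interpret, meaning failure to render the scripted dialogue between clinician and patient. Briefing the clinician and explaining one's role are the interpreter's own unscripted speech. On that reading only the accuracy marks of Domain 2 are waived in the opening and closing parts, and Domain 1 is still rated. Box 1 also lists the case briefing separately from the introduction to the patient. This reading is coherent, and because of it a reader who infers that Table 2 and the scoring sentence cannot both hold goes too far. But the protocol does not state the narrow reading, and it leaves Domain 1 without a source when the opening is absent from the footage.

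It can also be said that the two scoring sentences are simply a general rule and a named exception. That stands; they need not contradict each other. The difficulty lies in the undefined scope of the exception.

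Finally, the measures are to be completed by amendment. That defers their content, but the exemption is already fixed in the current text, so a later rubric must either limit it or carry the ambiguity forward.

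**Conclusion.** The point holds as a defect in a fixed scoring rule. The exemption is unrestricted, Domain 1 rests on video of the opening alone, and the text does not say how the two fit together. This rests on the inference from Box 1 that the briefing and role explanation fall in the opening parts. Its size and direction cannot be derived from the protocol.

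A reader might infer three stronger things that the document does not support.

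- **A power loss to 65%.** This requires Domain 1 to carry no effect for anyone at an unchanged SD. Removing the domain with its variance gives about 73% to 80% at 60 per arm for correlations from 0 to 0.5, against 81% planned.
- **A bias towards the training arm.** Outcome assessors are blinded and one rule applies to both arms. No omission or recording-loss rates are given. With invented rates of 10% of control and 2% of trained recordings losing half their marks, and the Section 5.5 means of 2.91 and 4.21, the shift would be 0.10 × 2.91/2 − 0.02 × 4.21/2 = 0.103 points, or 8% of 1.3. That still applies raw marks to a z-score outcome and lets a cut recording reduce the questionnaire-based parts, which it would not touch.
- **A rule that technical failures score zero while wholly missing recordings count as missing outcomes.** The protocol does not distinguish these cases. Awarding marks only for interpreted sections could also mean scoring from what is available.

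**What to change.** In the measures amendment already planned before any Study 2 data:

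1. Define the introductory and concluding components in terms of the Box 1 items, and map each item to the domains it informs.
2. Limit the exemption to parts that map to none of the six domains. If the mapping leaves no such part, delete the sentence.
3. State that Domain 1 is always scored from the briefing and introduction, and that a briefing or role explanation which the recording shows was not performed is scored as not performed.

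As a secondary clarification, have the blinded assessor code sections lost for technical reasons separately from sections that are present but not interpreted, so that the two can be handled differently in scoring and analysis.

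The cost is a sentence or two in Section 5.4, matching lines in the rubric and assessor training, and one extra code per recording. The sample size does not change.

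### Section 5.4 excuses failure to interpret the introductory component, yet Domain 1 of the primary composite is rated only from video, and its content sits in that opening part

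*Protocol*

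**What the plan says.** All of the relevant text is in section 5.4 of the protocol (Outcome measures).

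- **Outcome.** The quality of interpreted communication is "measured via a battery composite $z$ score evaluating six interpreting domains". No domain weights are given.
- **Domain 1 (Table 2).** "Pre-interactional briefing with clinician; explanation of role to clinician and limited English proficiency client". The only listed source is "Video footage rated by an experienced interpreter".
- **Layout of the simulation (Box 1).** It opens with "Case briefing between the clinician and interpreter (5mins") and then "Introduction to the patient (5mins"). The RUDAS and the questions on medical issues and mood follow. It closes with "Next steps (5mins").
- **Incomplete simulations.** Where parts of the simulation are missing or incomplete, "assessors will only award marks to the overall score for sections of the cognitive assessment that were interpreted". The next sentence makes an exception: "Failure to interpret the introductory or concluding component of the assessment will not affect the score".

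The protocol does not tie the terms introductory and concluding to the parts listed in Box 1. It does not say whether an excused part is credited, left out or rescaled when the composite is formed. The measures are to be developed after Study 1 and sent to the ethics committee as an amendment before Study 2 data collection.

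**The concern.** Table 2 says that briefing the clinician and explaining the role are part of what the primary outcome measures. The scoring rule says that leaving out the part of the simulation where at least some of this happens makes no difference to the score. Both cannot hold for the same behaviour.

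The interpreter's own dialogue is unscripted, so whether an interpreter explains the role to the client is observed behaviour that the outcome is meant to capture. Two things are at stake:

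- If trained interpreters do this more often than controls, excusing the omission removes part of a real difference between the arms.
- If the excused part is left out or rescaled, the composite is not the same quantity for every participant.

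Assessors could also read the sentence differently. The only double marking described covers each assessor's first four assessments, so a later divergence would probably not be noticed.

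**Working it through.** **1. Is there a figure in the plan to reproduce?** None on this point. The sample size section implies a standardised difference of 1.3 / 2.5 = 0.52, but for the score as a whole. It has no split by domain, so it cannot show how much of the effect Domain 1 carries.

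**2. Domain 1 set against Box 1 and the exemption.** The mapping to Box 1 is an inference from the wording, though a close one.

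| Element of Domain 1 | Natural place in Box 1 | Source other than video | If introductory means only the introduction to the patient | If it also covers the case briefing |
|---|---|---|---|---|
| Briefing with clinician | Case briefing | None | Scored | Excused |
| Role explained to clinician | Case briefing | None | Scored | Excused |
| Role explained to client | Introduction to the patient | None | Excused | Excused |

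The last row is excused on either reading. No later part of Box 1 is a natural place for an interpreter to explain the role to the client.

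**3. Share of the simulation.** Box 1 lists 5 + 5 + 15 + 5 + 5 = 35 minutes. The introductory component is 5 / 35 = 14% on the narrow reading and 10 / 35 = 29% on the wide one. These are shares of time. They are not shares of marks, because the protocol gives no marks per part.

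**4. Can another source stand in?** Domains 4, 5 and 6 combine video with a questionnaire, a scenario test or both. Domain 1 does not. If the opening is absent or excused, nothing else in the battery measures that content.

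**5. What the dilution depends on.** Suppose an excused interpreter is scored as if nothing had been left out. Compared with scoring the omission as observed, the loss in the difference between arms is then

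loss = w × (pC − pT) × d

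where w is the weight of Domain 1 in the composite, pC and pT are the proportions omitting the excused content in the control and trained arms, and d is the fall in the Domain 1 score that an omission would cause.

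- w: not in the protocol.
- pC and pT: not in the protocol.
- d: not in the protocol, and the marking guide is still to be written.
- Crediting the excused part: an assumption. If the part is left out or rescaled, the loss also depends on the participant's other domain scores.

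If pC = pT, the loss is zero. If pC > pT, as would be expected if training works on this behaviour, the loss is positive and the effect is understated. The direction is therefore conditional, and the size cannot be obtained from the documents.

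**The case against.** The strongest reply turns on the verb. To interpret is to render what others say, and Domain 1 is largely the interpreter's own speech. The case briefing takes place between clinician and interpreter, so there is nothing in it to render for a patient. The exemption may therefore concern only scripted opening and closing lines left unrendered, with Domain 1 scored as usual. This reading is tenable, and it is why the clinician briefing may well remain scored. It does not remove the conflict. The sentence exempts a whole component and says the score is unaffected, with no reservation for domain marks. An assessor following it as written would excuse the introduction to the patient, including the role explanation.

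Three further points stand:

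- The sentence belongs to a rule for missing or incomplete simulations. Domain 1 is still scored for interpreters who carry out the opening.
- The rule is the same in both arms and is applied by blinded assessors, so it does not by itself favour either arm.
- The measures are not final, and the planned ethics amendment is the natural place to settle the wording. That step will not correct the sentence unless someone changes it.

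A reader might also infer that the concluding exemption removes the dementia-related services content of Domain 4, through the next-steps part. The documents do not support this. Nothing assigns that content to the closing part, and Domain 4 also draws on a questionnaire.

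**Conclusion.** The conflict is real but limited. For simulations in which the opening is omitted, the rule as written excuses at least the role explanation to the client. It excuses all of Domain 1 if the introductory component includes the case briefing. If training increases this behaviour, the effect on the primary composite is diluted.

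This rests on two things: that Domain 1 content belongs in the opening parts of Box 1, and that the exemption is applied as worded.

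A reader might infer that one sixth of the primary outcome is exempt. That would need equal domain weights, exemption of the whole of Domain 1, and omission of the opening by every participant. The protocol states none of these. A reader might also wish to express the lost effect as a percentage of the planned 0.52. Any such figure would come entirely from assumed weights, omission rates and penalties, so none is given here.

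**What to change.** In section 5.4 and the marking guide:

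1. Define introductory and concluding component by naming the parts of Box 1 that each covers.
2. Limit the exemption to scripted opening and closing dialogue that carries no marks in any domain.
3. Score Domain 1 as observed whenever the interpreter is on the recording, so that an omission earns low marks. Treat Domain 1 as missing only when the footage itself is absent.
4. State that the same rule applies in both arms and at baseline, 3 months and 6 months.

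This amounts to rewording one sentence and adding an entry to the marking guide, before the measures go to the ethics committee in the amendment already planned. The exemption need not be deleted altogether. The downside is small: a few participants will have a low or missing Domain 1 score where they would otherwise have been excused.
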